#### Secondary endpoints

Primary analyses of the secondary endpoints replicate the computation of the models for the primary endpoint, as either ANCOVAs or logistic regressions (depending on the continuous or dichotomous scale of the respective endpoint). Group differences in the children’s attachment organisation (SSP/ AQS, binarised evaluation: secure/ insecure attachment), as well as all responder analyses (EAS sensitivity, EPDS, PRFQ, PSI at T1 and T2; SFS at T1, CBCL at T1 and T2), will be computed as logistic regressions adjusted for the stratification variable treatment setting with presentation of odds ratios. Should no cut-off values be available, dichotomous response variables for these measures will be computed using the Reliable Change Index (RCI; RCI > 1.96) [45]. Linear mixed models will be used to analyse the change in the secondary endpoints (maternal stress level, reflective functioning (PRFQ), and infantile symptoms) during the course of the study (12-months follow-up) across all measurement points.

Additional sensitivity analyses will be performed for health economic parameters as secondary endpoints, varying unit-cost assumptions for documented health care utilisation within realistic ranges. All secondary analyses of the primary and secondary endpoints are considered exploratory.

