### Secondary outcomes

#### Child attachment

The most important secondary outcome will be the child’s attachment style, measured using the Strange Situation Procedure (SSP) for children up to 20 months [31]. The SSP is a standardised procedure recording eight episodes to rate the child’s attachment quality to his or her caregiver. Attachment security is rated by independent coders blind to treatment allocation. The classification can be secure (B), avoidant (A), or ambivalent (C). Disorganised (D) attachment qualities will also be scored.

The attachment style of children older than 20 months is assessed using Attachment Q-Sort (AQS) [32]. The AQS evaluates the degree of attachment security for infants aged 12 to 48 months, and is a one- to two-hour procedure in which the child and its mother are observed in their home environment. The infant’s behaviour is evaluated by the observer for 90 standardised Q-Sort items, which are compared to a typical profile of securely attached children. The AQS varies on a scale between − 1 and 1, and does not reflect the variety of attachment categories, as the SSP does.

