#### Psychological factors

The Parental Stress Index (PSI) [43] is used to measure maternal parental stress, and the Parental Reflective Functioning Questionnaire (PRFQ) [44] to measure the mother’s self-reported ability to mentalise in the context of her relationship to her child. Both questionnaires are assessed at 6 weeks, and 12 months follow-up.

Additionally, the five further subscales of the EAS based on the 15-min videotaped mother-child interactions (maternal dimensions: structuring, non-intrusiveness and non-hostility; and child dimensions: responsiveness to parent, involvement with parent) are analysed as secondary outcomes. Free-play sessions are recorded at all measurement time-points and rated by reliable and independent coders blind to treatment allocation.

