#### Primary endpoint

The primary analysis of the primary endpoint (maternal sensitivity measured using the EAS subscale after 6 weeks) will be analysed using ANCOVA based on the FAS population using PIP versus CAU as the factor treatment group, EAS sensitivity at baseline as covariate, and the stratification variable treatment setting. Results will be displayed as adjusted means of the treatment group together with 95% confidence intervals and the respective *p* value (two-sided). The significance level is set at α =0.05. All further analysis is considered exploratory.

A secondary analysis of the primary endpoint will also be carried out using the ANCOVA model based on the PP population. Additional moderator analyses of the efficacy of PIP for a change in maternal sensitivity (EAS) will be conducted with treatment setting as the moderator, i.e. by additionally adding a ‘treatment group’ * ‘treatment setting’ interaction term to the model. Further moderator analyses regarding the efficacy of PIP will comprise maternal attachment type (AAI attachment) or maternal reflective functioning (AAI RF) as moderators.

In addition, models incorporating multiple imputation methods based on the PP population and a hierarchical regression model (including the therapist as a grouping factor and therapist’s adherence as covariate) will be used for sensitivity analyses of the primary outcome. To investigate the longitudinal change of the primary endpoint, linear mixed models (LMMs) incorporating both measurement points for each outcome (FAS population) will be computed. To explore further effects of additional predictors (such as the therapists carrying out the interventions), the models will be compared based on model fit values (AIC, the Akaike Information Criterion), with these predictors included in the model term.

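### The logistic models for responder and attachment endpoints name only treatment setting, in conflict with the preceding sentence on baseline, and carry no term for the two attachment instruments

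*Protocol article*

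**What the plan says.** All references are to the protocol article.

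- **General rule (Secondary endpoints).** "Primary analyses of the secondary endpoints replicate the computation of the models for the primary endpoint", as ANCOVAs or logistic regressions according to scale. The primary model (Primary endpoint) contains treatment group, "EAS sensitivity at baseline as covariate, and the stratification variable treatment setting".
- **Specific rule (next sentence).** Attachment and all responder analyses (EAS sensitivity, EPDS, PRFQ, PSI and CBCL at both follow-ups, SFS at the first) "will be computed as logistic regressions adjusted for the stratification variable treatment setting with presentation of odds ratios". Where a scale has no cut-off, response is defined by a Reliable Change Index above 1.96.
- **Baseline scores.** For the EAS, "Free-play sessions are recorded at all measurement time-points" (Psychological factors). The EPDS is taken at all measurement points (Maternal mental health problems). The CBCL is described as assessed again at the follow-ups, which implies an earlier assessment. The text lists PSI and PRFQ at 6 weeks and 12 months, and SFS at 6 weeks. The schedule figure is not in the text at hand.
- **Attachment.** The leading secondary outcome is "measured using the Strange Situation Procedure (SSP) for children up to 20 months"; older children get the AQS. The AQS runs from -1 to 1 and "does not reflect the variety of attachment categories, as the SSP does" (Child attachment). The analysed variable is "SSP/ AQS, binarised evaluation: secure/ insecure attachment". Aims and hypotheses ties it to the 12-month follow-up. No baseline attachment measurement is stated.
- **Status.** Everything beyond the primary analysis is called exploratory.

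**The concern.** Two adjacent sentences give different covariate sets for the responder models. Under the general rule the baseline score is in; under the specific rule it is not named. An analyst could defend either model after seeing the data, and the two give different odds ratios and different power.

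For attachment, one odds ratio covers two instruments. Which one a child receives depends on age, and age is not a stratification factor (Trial design lists setting and centre). If the proportion rated secure differs between instruments, a model without an instrument term leaves known variation unexplained, and its odds ratio averages over two ways of deciding who is secure. This outcome carries an explicit trial hypothesis, so a clear estimate matters even in an exploratory analysis.

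**Working it through.** **1. No figure to reproduce.** The protocol gives no power or sample size for these analyses. Sample size considerations supplies only the setting for the check: 64 per arm after dropout (80 × 0.80 = 64), d = 0.64 for the primary endpoint, and d = 0.44, which the plan uses for a moderator effect and which serves here only as a moderate effect size.

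**2. Both instruments will contribute.** Children enter up to 36 months of age and are seen again 12 months after baseline. A child enrolled above 20 - 12 = 8 months is past 20 months at that visit and gets the AQS; a younger one gets the SSP.

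**3. Responder models.** Assumptions, none of them in the protocol: a normal latent outcome with SD 1; baseline-outcome correlation r; response defined as exceeding a fixed cut-off of 0.25 SD, giving Φ(-0.25) = 40.1% control responders; 64 per arm; 2,000 simulated trials. Both models include setting; one adds the baseline score.

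Check on the setting-only odds ratio at d = 0.44: the treated rate is Φ(0.44 - 0.25) = Φ(0.19) = 57.5%, so OR = (0.575/0.425)/(0.401/0.599) = 2.02. The simulation gives 2.05.

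| d | r | Power, setting only | Power, plus baseline | OR, setting only | OR, plus baseline |
|---|---|---|---|---|---|
| 0.44 | 0.3 | 0.504 | 0.542 | 2.05 | 2.17 |
| 0.44 | 0.5 | 0.499 | 0.576 | 2.05 | 2.39 |
| 0.44 | 0.7 | 0.495 | 0.669 | 2.05 | 3.01 |
| 0.64 | 0.3 | 0.799 | 0.821 | 2.87 | 3.09 |
| 0.64 | 0.5 | 0.833 | 0.891 | 2.88 | 3.61 |
| 0.64 | 0.7 | 0.802 | 0.927 | 2.85 | 4.96 |

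With no effect, rejection is 0.048-0.051 without baseline and 0.043-0.052 with it.

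**4. Attachment model.** Assumptions: half the children on each instrument, a true odds ratio of 2.5 within each, 64 per arm, 2,000 trials. For simplicity setting is left out of both models.

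| Control secure rate, SSP / AQS | Power, pooled | Power, with instrument | OR, pooled | OR, with instrument |
|---|---|---|---|---|
| 50% / 50% | 0.720 | 0.716 | 2.53 | 2.55 |
| 40% / 60% | 0.681 | 0.698 | 2.48 | 2.60 |
| 30% / 70% | 0.576 | 0.631 | 2.22 | 2.58 |

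Check on the last row: treated odds are (0.30/0.70) × 2.5 = 1.071 and (0.70/0.30) × 2.5 = 5.833, so the rates are 0.517 and 0.854, mean 0.685. The control mean is 0.50, with odds 1. The pooled OR is therefore 0.685/0.315 = 2.18, close to the simulated 2.22.

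With no effect, rejection is about 0.04-0.06 with or without the instrument term.

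**The case against.** The strongest reply is that baseline is not omitted at all: the general rule already brings the primary model's covariates into the logistic regressions, and the next sentence merely mentions setting. That reading is possible, which is why the point is an inconsistency to reconcile and not a proven omission.

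It is also fair to say that a setting-only odds ratio is a legitimate marginal quantity. Adding a prognostic covariate to a logistic model changes the estimand to a conditional odds ratio. Power rises because that ratio lies further from 1, not because its standard error shrinks. This stands, and is a reason to state which quantity is meant.

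Several stronger readings are tempting, but the document does not support them:

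- *The attachment model drops a collected baseline value.* No baseline attachment measurement is stated, so there is none to add.
- *Baseline exists for every responder scale.* The text does not confirm it for PSI, PRFQ or SFS.
- *Dyads count as responders without changing.* The article does not say how a cut-off becomes a response, and may leave this to the full protocol. Responders defined by the Reliable Change Index already use baseline.
- *A raw continuous score is pooled with categories.* The AQS is binarised before it is combined. Secure against insecure does not need the further SSP categories.
- *Age imbalance biases the attachment result.* Instrument depends on age, not on arm. A 10-20 point difference in secure rates times a 10-20 point imbalance shifts the difference by 1-4 points (0.1 × 0.1 to 0.2 × 0.2). The standard error of a difference at 64 per arm is √(2 × 0.25/64) = 8.8 points. A 20-point imbalance would itself be 20/8.8 = 2.3 standard errors if half the children used each instrument.

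Finally, these analyses are exploratory, and ANCOVAs and mixed models are planned alongside them. That limits the weight of the point but does not settle which logistic model is meant.

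**Conclusion.** The point holds in a limited form. The protocol's two sentences disagree on whether the responder models include baseline, and the combined attachment endpoint has no term for instrument. The cost is power and a less clearly defined odds ratio. A reader might infer bias or false-positive inflation; randomisation rules out systematic bias, and the simulations show no inflation.

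On the assumptions above, including baseline takes responder power at d = 0.44 from about 0.50 to 0.54-0.67 for r of 0.3-0.7, and at d = 0.64 from 0.80-0.83 to 0.82-0.93. These gains apply to cut-off-defined response; they were not calculated for response defined by reliable change. The instrument term adds roughly 0 to 5 points, with the upper end only if secure rates differ as strongly as 30% against 70%. The protocol gives no correlations, responder rates or secure rates by instrument, so the sizes are illustrative. The inconsistency itself rests on the text alone.

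**What to change.** 1. Reconcile the two sentences under Secondary endpoints. State that each responder model contains treatment group, treatment setting and the baseline score of the same scale wherever it is collected: EAS sensitivity and EPDS explicitly, CBCL by implication, and PSI, PRFQ and SFS if the schedule confirms a baseline assessment.
2. For the 12-month secure/insecure endpoint, add instrument (SSP or AQS, equivalent to age band) as a covariate beside setting, and tabulate secure rates by arm within each instrument descriptively. Fully separate analyses are not required; they would split an already small sample.
3. Say that the reported odds ratios are conditional on these covariates.

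The cost is small: a wording change, one extra covariate per model and one descriptive table, with no new data. Two consequences should be accepted openly. The adjusted odds ratio is conditional and will usually lie further from 1 than the marginal one. Because the primary analyses do not impute (Missing data), dyads lacking the baseline score drop out of the adjusted model.

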#### Missing data

After written informed consent and randomisation, participants can be excluded from the analyses only if there has not been any intervention, no data have been collected after randomisation, or at the participants’ express request after withdrawing from the study during the data collection phase. Primary statistical analyses of the primary and secondary endpoints are based on the FAS population without the imputation of missing data. For a sensitivity analysis, missing values for the primary endpoint will be imputed using Multiple Imputation methods for linear regression based on Markov chain Monte Carlo (MCMC) simulations. Imputation variables will be selected blinded for the intervention groups, and at least 5000 iterations and 100 imputations will be calculated.

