### Data analyses

#### General considerations and socio-demographic data

Socio-demographic and clinical information are described at baseline using frequencies and percentages (e.g. categorical variables) or means and standard deviations (e.g. continuous variables), and treatment conditions compared to assess potential baseline differences. The statistical analyses are based on all mother-child dyads included in the study after randomisation (Fig. 1), according to ITT (Intention to Treat) principles. The data to be used in all analyses (unless otherwise stated) is defined as the Full Analysis Set (FAS) and includes all mother-child dyads after randomisation, irrespective of the treatment received. Data from mother-child dyads who drop out of the study are included in the FAS up to the date they withdraw. The Per Protocol (PP) population is a subset of the FAS and includes mother-child dyads who conform to the study plan (i.e. sufficient treatment adherence, no major protocol violations). The safety population is defined as mother-child dyads who have participated in at least one intervention session, and is analysed according to the treatment they received.

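### The missing-data rule allows a randomised dyad to be excluded only because it had no intervention, contradicting the intention-to-treat Full Analysis Set used for the primary test

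*Protocol article*

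**What the plan says.** Three sections of the protocol article bear on who is in the primary analysis.

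- **General considerations and socio-demographic data.** The analyses are to be run "according to ITT (Intention to Treat) principles". The FAS, the default for all analyses, "includes all mother-child dyads after randomisation, irrespective of the treatment received". For dropouts: "Data from mother-child dyads who drop out of the study are included in the FAS up to the date they withdraw". Receipt of treatment is a condition of entry for one set only: "The safety population is defined as mother-child dyads who have participated in at least one intervention session". The per-protocol set is a subset of the FAS, chosen on adherence and absence of major violations.
- **Primary endpoint.** Maternal sensitivity at 6 weeks "will be analysed using ANCOVA based on the FAS population using PIP versus CAU as the factor treatment group". Everything beyond this analysis is called exploratory.
- **Missing data.** Once a dyad is randomised, the rule is that "participants can be excluded from the analyses only if there has not been any intervention, no data have been collected after randomisation". A third ground, joined to these two by *or*, is a wish to be excluded voiced by someone who has withdrawn. The next sentence bases the primary analyses on the FAS, without imputation.

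**The concern.** A dyad that was randomised and received nothing is in the FAS under one section and removable under another. Two analysts following this document could run the confirmatory test on different populations.

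The choice matters because treatment is open. The dyad knows its arm before the first session, so the decision not to start can depend on the allocation. Failing to start is easy to recognise for PIP, a fixed course of 12 sessions. It is less clear-cut for care as usual, which the protocol describes as varying in number and intensity. Removing never-treated dyads can therefore take different kinds of dyads from the two arms. Blinded rating of the videos protects the measurement of the outcome, but not the selection of who is measured. Because the rule permits exclusion without requiring it, it also leaves room for a choice made after the data are known.

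**Working it through.** **Step 1: is the conflict real?** Take a dyad that was randomised, had no intervention and returned for the 6-week EAS video.

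- FAS definition: included, because treatment received is irrelevant.
- Missing data section: may be excluded. The three grounds are joined by *or*, so the first is sufficient alone.
- Could the rule be meant only for the per-protocol or safety set? It refers to the analyses in general, and the following sentence concerns the FAS.
- Could the first ground merely restate that dyads without data cannot be analysed? That is the second ground. The first adds something only for untreated dyads that do have data.

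The two sections disagree about this dyad, and no other section settles it.

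**Step 2: which dyads does it affect?** The primary ANCOVA does not impute. A never-treated dyad without a 6-week EAS drops out of the model whatever the exclusion rule says. Only those that never start *and* have a 6-week EAS are at issue.

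**Step 3: how large could the bias be?** The plan states no figure to reproduce. Assumed inputs:

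- q: share of PIP dyads with a 6-week EAS that are excluded as never treated.
- g: how far their outcome lies below that of the other PIP dyads, in SD, after baseline adjustment.
- No CAU dyad is excluded.

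Let m be the mean of the PIP dyads that are kept. The mean of all PIP dyads is (1 − q)m + q(m − g) = m − qg. Excluding the never-treated raises the PIP mean from m − qg to m, so

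bias = q × g.

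| q | g | Bias (SD) | Share of the planned d = 0.64 |
|---|---|---|---|
| 5% | 0.3 | 0.05 × 0.3 = 0.015 | 0.015/0.64 = 2% |
| 10% | 0.5 | 0.10 × 0.5 = 0.05 | 0.05/0.64 = 8% |
| any | 0 | 0 | 0% |

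The bias is also zero if excluded dyads are equally frequent and alike in both arms. If g is negative, the effect is understated instead.

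**Step 4: effect on the test.** Take the planned 80 per arm, all with outcomes, SD 1, no true effect and a two-sided normal test at 0.05. For q = 10%, g = 0.5:

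- PIP dyads kept: 80 × 0.9 = 72.
- Standard error: √(1/72 + 1/80) = 0.162.
- Shift: 0.05/0.162 = 0.31 standard errors.
- Type I error: 1 − Φ(1.96 − 0.31) + Φ(−1.96 − 0.31) = 0.061.

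For q = 5%, g = 0.3, the standard error is √(1/76 + 1/80) = 0.160, the shift is 0.015/0.160 = 0.09, and the type I error is about 0.051.

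**The case against.** The best defence is that the sentence limits exclusions. It says when they are allowed and requires none. The FAS definition, the Primary endpoint section and the sentence that follows it all point to analysis of every randomised dyad. This stands as far as it goes: the document does not commit the trial to a biased comparison. It does not remove the conflict, since an exclusion that the FAS definition forbids is still expressly allowed.

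A reader might infer more than the text supports:

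- *That the primary comparison becomes PIP starters against users of some usual care.* That is one possible application of a permissive rule.
- *That no intervention cannot be determined under care as usual.* The control group section says individual interventions will be documented in detail, so it can be checked from records. Zero CAU exclusions is an assumption made here, and it is the unfavourable case.
- *That the share affected could be as high as 20%.* That equals the whole drop-out rate assumed in the sample size section, whereas the dyads at issue are those who did return at 6 weeks. The relevant q should be smaller.
- *That the safety set, requiring "mother-child dyads who have participated in at least one intervention session", shows the same fault.* It is an as-treated set by design and does not feed the primary test.
- *That imputation on the FAS would repair the problem.* The protocol specifies none: the Primary endpoint section ties multiple imputation to the per-protocol population, and the Missing data section offers imputation only as a sensitivity analysis.

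**Conclusion.** The point holds as a contradiction about the population for the one confirmatory test. It needs correction as written and does not depend on any assumed figure.

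The consequence is that the rule *can* bias the comparison. Neither the size nor the direction can be taken from the documents, which give no non-start rate and nothing on how such dyads differ. With all exclusions in the PIP arm and lower outcomes among those excluded, the illustrative overstatement is 0.015 to 0.05 SD, or 2% to 8% of the planned effect, with type I error of about 0.051 to 0.061. That is modest, and it vanishes if the excluded dyads do not differ or are balanced and alike across arms.

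**What to change.** In the Missing data section, delete the absence of any intervention as a ground for exclusion, or confine it explicitly to the per-protocol and safety sets. Add that every randomised dyad with a 6-week EAS is analysed in its randomised arm, whatever treatment it received, except where the participant expressly asks to be excluded. The ground concerning absence of post-randomisation data can stay, since such dyads cannot enter an ANCOVA without imputation.

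The cost is about one sentence, to be settled before the intervention data are unblinded. The sample size stays at 160. Dyads that do not start must still be invited to the 6-week assessment, which the stated intention-to-treat principle already implies.
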